### Participating primary care staff

Primary care staff members including physicians, nurses, mental health staff, and management at each PCC will be provided with written information about the study. Those who agree to participate will complete questionnaires assessing work environment and PCBH implementation aspects and may be invited to participate in focus groups.

### Measures and assessments

Measures and assessments are categorized into implementation, organization, and patient levels. These will be collected through administrative systems, medical records, national registers, staff and patient self-report forms (primarily via a digital platform, via phone when needed) as well as semi-structured interviews conducted by independent research personnel. Table 1 provides an overview of all patient-level self-report questionnaires and timepoints. To enhance participant retention, automated text message reminders are sent for each assessment. Trained research assistants will also proactively contact patients who have not completed their assessments via phone. For participants who wish to discontinue due to time constraints, the option of completing a shorter assessment that includes the most important questionnaires will be provided. As a final option, they will be given the opportunity to complete only the primary patient outcome assessment over the phone.

### Implementation outcomes

#### Overall categorical PCBH model fidelity

To assess fidelity, implementation measures (see Model adherence, obstacles, and facilitators) and semi-structured interviews with PCC managers will be used. Three fidelity levels are established: FID1 represents no PCBH implementation, FID2 represents partial PCBH implementation, and FID3 represents adequate PCBH implementation. Two of the authors ([name], [name]), along with independent PCBH experts and supervisors, will determine the timepoints when each PCC transitions between fidelity levels. The primary outcome is the time taken for a PCC to reach FID3 level. Secondary outcomes include whether a PCC reaches FID3 within the preset implementation period and the time taken to reach FID2 level. These categories will be used as a base for some analyses, including the primary analysis for organizational and patient level data (see Data Analysis Plan).

#### Implementation success

The s-NoMAD questionnaire, which evaluates the integration of complex interventions into daily practice [65], will be administered to nurses, physicians, mental health workers, and leaders to assess implementation success.

#### Acceptability, appropriateness and feasibility

The Acceptability of Intervention Measure (AIM), Intervention Appropriateness Measure (IAM), and Feasibility of Intervention Measure (FIM) [66] are four-item measures of implementation outcomes that are considered particularly relevant to implementation success [67]. Profession-specific versions of these will be administered to nurses, physicians, mental health workers and leaders, focusing on key elements of the PCBH model that are particularly relevant to their daily work.

#### Model adherence, obstacles, and facilitators

Average Appointment Length (AAL) assesses the average duration of bookable appointments in mental health workers’ schedules, measured in minutes.Supply of Appointments (SA) measures the number of bookable appointments available per full-time mental health worker on a weekly basis and reflects the capacity and availability of PCBH services.Future Capacity (FC) indicates the number of available timeslots for appointments in the coming 4 weeks divided by the total number of timeslots in mental health staff schedules. It provides insights into the PCC’s ability to accommodate new patients.Percentage Longer Treatments (PLT) indicates the proportion of patients who have exceeded the standard number of visits (more than 4), signaling a departure from usual PCBH routine.The Primary Care Behavioral Health Provider Adherence Questionnaire (PPAQ) [68] assesses the adherence of behavioral health providers to the PCBH model. For this study, it was adapted for the Swedish setting, incorporating forward and backward translation, the addition of new items, and the removal of irrelevant items. To address the teamwork aspect of PCBH, similar questionnaires were developed for physicians and nurses in collaboration with Swedish PCBH experts, utilizing item-level Content Validity Index ratings [69]. The resulting scales are named Integrated Behaviors in Primary Care for General Practitioners / Mental Health / Registered Nurses (IBPC-GP, -MH, -RN).Levels of Integration Measure (LIM) [70] evaluates healthcare leaders’ perception of the PCC’s integration level regarding behavioral health staff. Similar to the PPAQ, adaptations have been made to reflect its use in the Swedish healthcare system.

In addition to these measures, PCBH supervisors will provide ratings and structured qualitative descriptions of each PCC’s progress in the implementation process after every supervision meeting. This feedback will capture the supervisors’ perspectives on obstacles and facilitators encountered during the local implementation processes.

.

### Organizational outcomes

#### Measures relevant to patient reach

The penetration rate indicates the number of unique patients seen per full-time equivalent mental health professional and will be measured in relation to all listed patients (PR1) as well as patients with a mental health diagnosis (PR2).

#### Work environment and teamwork among staff

To evaluate any changes in staff work environment, 35 items from the Copenhagen Psychosocial Questionnaire (COPSOQ-III) [71], a measure of psychosocial work environment, will be administered to participating staff. The subscales of Consensus and Collaboration of the IBPC-GP, -RN and -MH scales will be used to measure teamwork at the PCC.

#### Measures relevant of access of care and wait times

Average waiting time (AWT, primary organizational outcome) captures the waiting time from the identification of a behavioral health concern to being seen by any clinician. It includes the time between the patient’s initial contact (phone call or message) and the visit with any clinician. If the concern is identified during another visit, the wait time is calculated from the visit where the need was identified to the visit with the referred-to profession.Average waiting time for a psychosocial intervention (AWT-P) focuses specifically on the waiting time from the identification of a behavioral health concern to receiving any mental health intervention.Number of individuals on waiting lists to receive psychosocial interventions (WL).Third Next Available Appointment (TNAA) assesses the waiting time until the third next available appointment for a hypothetical patient who contacts the PCC on a given day. It is measured consistently at the same time every week (e.g., Mondays at 9 AM). TNAA provides insights into the access and availability of care, independent of patients’ own ability to show up at a given time.Average number of visits and phone/video contacts during patients’ period of care.

#### Cost, health economics and utilization of medication and sick leave

Utilization of medical care and productivity losses will be measured using the Trimbos and iMTA questionnaire on Costs associated with Psychiatric Illness (TiC-P). This includes assessing the number of days on sick leave, productivity loss while at work, productivity loss at home, and medications prescribed and taken. The 5-item Eq. 5D will be administered for health economic evaluations. Cancelled Visits and No-Shows (CVNS) will be tracked, capturing the number of visits where patients either cancelled late or did not show up. Specialist Referrals (SR) will be recorded as the percentage of patients referred to specialized care and Denied Referrals (DR) will indicate how many of these referrals were not accepted. Patient self-reports will be complemented and combined with national register-level data on sick leave, medications, and health care utilization.

### Patient outcomes

The main time-points for all non-register patient measurements are as follows:

Before or shortly after first contact with the PCC. This is considered the pre-measure timepoint.4-week follow-up (FU4).8-week follow-up (FU8).12-week follow-up (FU12). This timepoint is considered post-measure when applicable.One year follow-up (FU52).

#### Sociodemographic and clinical data

Social and economic status, education, profession, and employment/activity status will be collected through self-report. The main reason for the visit, the duration of the problem, other health concerns, concomitant care, care consumption, ICD-10 diagnoses and medications will be captured through self-reports and medical records.

#### Everyday functioning, symptoms, and quality of life

The primary patient outcome is everyday functioning, assessed through four domains (8 out of 12 items) of the WHO Disability Assessment Schedule 2.0 (WHODAS-12) [72]: Life activities, Cognition, Getting along, and Participation. The domains of Mobility and Self-care, which form independent factors and are not expected to change significantly, will be excluded from primary analyses but considered in secondary analyses. A range of very short versions of well-established patient-rated scales for common mental health conditions will be used to measure symptoms. For an overview, see Table 1. Each scale will be used to evaluate changes to the specific symptoms measured, as well as for dividing patients into different analysis groups based on problem areas. Additionally, a total index for symptom load will be calculated from all 21 items, with appropriate weighting to account for the varying number of questions across domains. Quality of Life will be measured by the 12-item Brunnsviken Brief Quality of Life (BBQ) [73], which examines the importance and fulfilment of six areas (e.g. spare time quality, creative work, and friendship). Additionally, the 4-item Outcome Rating Scale (ORS) [74] will be used. Complementing these measures is the DAily Routines for Well-being INventory (DARWIN), developed by the research group, which evaluates the frequency of 11 behaviors relevant to mental health, including exercise, regular eating, socializing, and sleep hygiene.

**Table 1 Tab1:** Overview of patient self-report questionnaires measuring symptoms, including timepoints

Questionnaires measuring symptoms	Initial visit	FU4	FU8	FU12	FU52
Patient Health Questionnaire 9-item (PHQ-9)^1^	X			X	X
Generalized Anxiety Disorder 7-item (GAD-7)^1^	X			X	X
Patient Health Questionnaire 4-item (PHQ-4)^1^		X	X		
Panic Disorder Severity Scale 2-item (PDSS-SR-2)^2^	X	X	X	X	X
Social Phobia Inventory – Abbreviated Version (Mini-SPIN-3)^1^	X	X	X	X	X
Obsessive Compulsive Disorder 3-item (OCD-3)^3^	X	X	X	X	X
Perceived Stress Scale 2-item (PSS-2)^1^	X	X	X	X	X
One-item question on perceived stress^3^	X	X	X	X	X
Karolinska Exhaustion Disorder Scale 3-item (KEDS-3)^3^	X	X	X	X	X
Insomnia Severity Index 2-item (ISI-2)^1^	X	X	X	X	X
Short Health Anxiety Inventory 3-item (SHAI-3)^2^	X	X	X	X	X
The Alcohol Use Disorders Identification Test-Concise (AUDIT-C-3)^1^	X	X	X	X	X
Pain (One-item rating from 0 to 10)^3^	X	X	X	X	X

^1^ Published and empirically tested.

^2^ Created by factor analytic item-reduction and sensitivity to change analyses on large datasets from previous trials conducted by the research group, not yet published.

^3^ Created by an expert group, not yet published or empirically tested.

#### Change, adverse events and satisfaction with care

Patient experiences and perceptions will be assessed using multiple measures. Satisfaction will be evaluated using 4 items from the Client Satisfaction Questionnaire (CSQ) [75], the Session Rating Scale (SRS) [76], and 9 additional items specifically designed for PCBH settings to gauge patients’ perceptions of and attitudes toward their care providers. To measure subjective change, the one-item Patient Global Impression - Improvement (PGI-I) [77] scale will be employed. To assess treatment side effects, an Adverse Events questionnaire will be employed, offering both a concise (3 items) and a more extensive version (9 items) at different timepoints, in which patients will have the opportunity to report and describe any unwanted treatment effects or events they may have experienced. Additionally, at the FU12 timepoint, patients will be offered the opportunity to participate in semi-structured interviews to provide detailed insights on their satisfaction, adverse events, treatment content, goals, and perceived changes in symptoms and quality of life. Any adverse events that require immediate action will be reported to the responsible PCC.

#### Treatment content

Information on which interventions are used within each primary care model will be obtained through medical records. In addition, patients will be asked in interview form what interventions they remember and which strategies they use after treatment.

### Primary care models

#### Care as usual (CAU)

CAU refers to the currently most common way of organizing behavioral and psychological care in Sweden. In accordance with this, all CAU centers, in this study the DELAYED arm, will have on-site clinical psychologists or social workers delivering a variety of talking treatments. Crucially, these functions will not be integrated into the PCC’s workflow but will function as co-located mental health services, in line with the traditional model for delivering psychosocial interventions [19]. Typical routines at CAU centers will involve written referrals from physicians, no direct triage to mental health services and caregivers managing their own schedules and bookings. Interdisciplinary collaboration, if present, is typically done only through scheduled team conferences. Productivity as well as the reach of interventions in relation to mental health is ordinarily low, resulting in extensive wait times and queued referrals. The content of psychological treatment within the CAU model will vary depending on the staff present at each PCC, from supportive counseling to manualized CBT and long-term psychodynamic psychotherapies. The actual content of an individual patient’s care will be assessed retroactively through medical records. Semi-structured interviews with PCC managers will be used to assess that no PCCs in the CAU condition have workflows that are reminiscent of PCBH.

#### Primary Care Behavioral Health (PCBH)

An obstacle to high quality PCBH research is that there is a variation in the understanding of the aim and key strategies of the model [59]. In this project, a version of the PCBH model adjusted for the Swedish health care system [15] will be used. The focus of the implementation effort is to increase access and decrease wait times for mental health interventions as well as increase collaboration between psychologists/social workers and medical staff. The planned changes include introducing direct triage, same-day appointments, clinical pathways, and a stepped care model for interventions as well as shortening appointment lengths and increasing productivity. Importantly, the typical PCBH routine of ‘warm hand-offs’ (patients being offered a visit with a mental health professional directly after a visit with a primary care physician) [22] will not be emphasized, as Swedish health care increasingly leans on direct triage, where the physician visit is postponed or replaced entirely [78]. Another aim is to increase the efficiency of interprofessional collaboration by defining and clarifying the role of the mental health staff, educating other professions in when and how to utilize their services as well as introducing a common language and mindset for discussing mental health issues with both patients and colleagues. Routine coordination, efforts to reach a shared understanding among staff and quick ‘curbside consultations’ will be emphasized over scheduled team conferences. Mental health staff will be taught to assess patients’ problems through a contextual rather than a medical model of mental health and administer brief interventions adapted to the patients’ problem and life situation, as described in the introduction. All mental health staff will receive three days of training followed by six 4-hour supervision sessions over the course of six months. Training and supervision will focus on both organizational and clinical aspects of the model. Additional support for individual PCCs will be considered in the case of low model fidelity. A local implementation group will be established at each PCC, consisting of all mental health staff, managers as well as representatives for physicians, nurses, and other relevant occupations. All other staff will receive 2 hours of training. All training and supervision will be conducted by an external part. One of the authors ([name]) will together with research assistants oversee adherence by monitoring implementation outcomes (see Model adherence, obstacles, and facilitators) and giving feedback and recommendations to PCC managers and PCBH supervisors. No additional auditing is planned.

### Data management, monitoring and confidentiality

Data will primarily be collected through and stored in encrypted form in the study technical platform and database (BASS4) provided by Karolinska Core Facilities. Patients and staff fill in questionnaires online. Data are then stored behind two-factor verification and accessible only to selected research personnel. Data collected through means other than self-report forms will be manually entered into BASS4 by research assistants. All data entry is done in premade templates, ensuring that data are in a proper format and within an expected range of values. Any data coding is done according to standardized coding practices. When data collection is finished, all data will be pseudonymized and key coded. Only the principal investigator and university archivists will be able to access the key. Other project team members will only be able to access pseudonymized data. Considering the nature of the trial, which primarily involves data collection from routine clinical practice and presents a low anticipated risk to participants and given that data monitoring for psychological intervention trials is not mandatory in Sweden, we decided to forgo a data monitoring committee due to costs.

### Data analysis plan

We are planning to conduct one main analysis for each of the primary outcomes at each level, a range of explorative and longitudinal analyses for the implementation-level outcomes, and several secondary analyses for the organizational- and patient-level outcomes. Primarily, we aim to confirm that the EARLY arm reaches adequate fidelity level faster than the DELAYED arm and to capture the randomized controlled effects of PCBH on organization- and patient-level outcomes when it has reached adequate model fidelity during the first implementation period (corresponding to an implemented-per-protocol perspective). We also want to evaluate the controlled effects of intending to implement PCBH regardless of what level of fidelity each PCC reaches (corresponding to an intent-to-implement perspective) and the non-controlled (i.e., not comparing the randomized groups) relation between reaching adequate model fidelity and outcomes (corresponding to an adherence-effect or dose-response perspective). No interim analyses are planned.

Implemented-per-protocol analyses:

PCCs in EARLY, from when they have reached FID3, compared to all PCCs in DELAYED, during period 1 (main analysis).As (1), but also including data from period 2 in EARLY (but not in DELAYED), to control for the event of PCCs needing extended time to reach FID3, thus lowering the power of the main analysis.

Intent-to-implement analyses:

3.All PCCs regardless of model fidelity in EARLY compared to all PCCs in DELAYED during period 1.4.As (3), but for periods 1 and 2.

Adherence-response analyses (not controlled by randomization):

5.All PCCs, regardless of arm, when in FID3 during period 1 or 2, compared to PCCs in DELAYED during period 1.6.As (5), but compared to all PCCs before they reach FID3.

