## Methods/design

The main purpose of the current project is to strengthen the evidence base for PCBH regarding implementation-, organization-, and patient-level outcomes by conducting the first large-scale randomized study on the model, taking a step toward answering whether the effects of the model are large enough to merit scaling up implementation. The research questions of primary interest are divided into three levels, where outcomes of higher levels are more or less dependent on the lower levels (i.e., patient outcomes may be dependent on organizational outcomes and both are clearly dependent on implementation outcomes; see Fig. 1):

Implementation level:
What is the timeline for partial implementation (FID2) as well as achieving adequate model fidelity (FID3, primary implementation level outcome) in PCCs adopting the PCBH model?How do healthcare staff perceive the acceptability, feasibility, and appropriateness of PCBH, and to what extent do they adhere to the model?What are the observed obstacles and facilitators during implementation?
Organizational level:
Is PCBH superior to traditional Swedish primary care in reducing waiting times (primary organization level outcome) and increasing patient reach?Does PCBH result in shorter treatment lengths and lower costs for staff and resources compared to traditional primary care?Does PCBH improve interprofessional collaboration and staff work environment compared to traditional care?Does PCBH impact medication prescription patterns, sick leave utilization, and patients’ care consumption, thereby influencing related costs?
Patient level:
Is PCBH superior to traditional Swedish primary care in terms of patient outcomes, including everyday functioning (primary patient level outcome), symptoms, quality of life, satisfaction with care, subjective change, and adverse events?If not superior, is PCBH non-inferior to traditional primary care?What methods are used within brief interventions and what strategies do patients adopt after treatment?

The primary comparisons between PCBH and traditional primary care will consider model fidelity at both the organizational and patient levels. The main analysis will compare PCCs randomized to the early implementation arm once they reach satisfactory fidelity with PCCs in the control group.

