## Discussion

The main purpose of the current project is to strengthen the evidence base for the effects that PCBH has on implementation-, organization-, and patient-level outcomes. Implementation of a primary care model such as PCBH needs to be studied in a naturalistic setting, which reduces the possibility for rigorous research procedures and high levels of control. In addition, implementing PCBH is a large undertaking that requires systematic changes on both an organizational and an individual level – processes that are highly dependent on the local context and difficult to control. The implementation in this study is initiated by an external stakeholder, Närhälsan, and performed by a publicly procured company. As such, we as researchers have little control over the specifics of training and supervision, as well as over which PCCs participate in the project, how these are chosen, and their internal contexts and readiness for change. This means that the model fidelity categorization is an essential aspect – especially as many measurements and analyses are hierarchically dependent on each other. Patient outcomes (such as everyday functioning and satisfaction with care) may be partly dependent on organizational outcomes (such as waiting time until first visit) and they are both dependent on implementation outcomes (such as acceptance of and adherence to PCBH routines).

We have designed this study in an effort to evaluate the causal effects of PCBH despite these complex aspects. We have identified relevant measures and divided them into the three hierarchical levels described above. The data analysis plan has been designed to primarily utilize the randomized controlled design from both a per-protocol perspective (focusing on PCCs with successful implementation) and an intent-to-implement perspective (focusing on all PCCs in the EARLY implementation group regardless of which model fidelity category they reach). These analyses are complemented by secondary analyses based only on model fidelity and its association with outcomes, ignoring the randomized design but providing an opportunity of an equivalent of a dose-response analysis. Finally, in case we do not establish superiority for PCBH on the patient-level primary outcome, we will also execute non-inferiority analyses. In total, this results in a large number of planned analyses, but we deem this to be necessary to manage the complexities described above.

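### The main organisational and patient-level analysis filters only the EARLY arm on fidelity judged after randomisation, so it is not the randomised comparison the plan says it is

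*Protocol article*

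**What the plan says.** The Methods/design section states that "The main analysis will compare PCCs randomized to the early implementation arm once they reach satisfactory fidelity with PCCs in the control group". The Data analysis plan lists this as analysis 1: "PCCs in EARLY, from when they have reached FID3, compared to all PCCs in DELAYED, during period 1 (main analysis". The stated aim is to "capture the randomized controlled effects of PCBH on organization- and patient-level outcomes when it has reached adequate model fidelity during the first implementation period", which the same sentence describes as "corresponding to an implemented-per-protocol perspective".

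Analysis 2 extends the EARLY data into period 2. Analyses 3 and 4, called intent-to-implement, compare all EARLY with all DELAYED centres regardless of fidelity. Only analyses 5 and 6 carry a warning, under the label "Adherence-response analyses (not controlled by randomization".

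On how FID3 is set, the section on overall categorical fidelity says that two of the authors, "along with independent PCBH experts and supervisors, will determine the timepoints when each PCC transitions between fidelity levels". The Sensitivity analyses section concedes that there is no objective cutoff for adequate PCBH. The Discussion says that implementation depends on local context, and that the researchers have little control over training and supervision, "as well as over which PCCs participate in the project, how these are chosen, and their internal contexts and readiness for change".

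**The concern.** Randomisation makes the 17 centres comparable as assigned. Analysis 1 then removes centres and patients from one arm by a judgement made after assignment. DELAYED centres that would have been slow or unable to reach FID3 stay in, because they have not started and cannot be identified. What remains is EARLY centres that implemented successfully against unselected DELAYED centres.

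The selection need not be unrelated to outcome. Reaching FID3 depends on local context. The fidelity judgement also draws on the model-adherence measures, among them Future Capacity and Supply of Appointments. These are scheduling measures close to average waiting time, the primary organisational outcome, so for that outcome selecting on fidelity may partly be selecting on the result.

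At stake is how the headline result is read at two of the three outcome levels. The implementation-level question, time to FID3 in EARLY versus DELAYED, is compared as randomised and is not affected.

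**Working it through.** **1. Which data enter, by arm (period 1)**

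| | EARLY | DELAYED |
|---|---|---|
| Analysis 1 (main) | Centres reaching FID3, from that date | All centres, no stated restriction |
| Analysis 3 | All centres | All centres |

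Only analysis 3 keeps the arms as assigned throughout. The planned sensitivity analysis that also counts FID2 as adequate moves the cutoff but keeps the one-arm filter.

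**2. Size of the selection bias with no PCBH effect**

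Assumptions, none of them in the documents: EARLY is the arm with 8 centres (the power section does not say which arm has 8); 5 of the 8 reach FID3; those 5 rank highest on a normally distributed readiness trait; and that trait correlates ρ with the centre's own outcome level.

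The expected mean of the top 5 of 8 standard normal values is (1.424 + 0.852 + 0.473 + 0.153 − 0.153)/5 = 0.55. Bias in between-centre SD is 0.55 × ρ. With ICC 0.01 (from the power section) the between-centre SD is √0.01 = 0.1 patient SD.

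| ρ | Bias, between-centre SD | Bias, patient SD at ICC 0.01 |
|---|---|---|
| 0.5 | 0.27 | 0.03 |
| 0.7 | 0.38 | 0.04 |
| 0.9 | 0.49 | 0.05 |

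**3. False positives favouring PCBH (nominal 2.5%, pooled t test on centre means, 5 + 9 − 2 = 12 df, simulated)**

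- WHODAS, with 476/17 = 28 patients per centre. The variance of a centre mean is 0.01 + 0.99/28 = 0.0454, so SE = √[0.0454 × (1/5 + 1/9)] = 0.119. The bias is 0.03/0.119 to 0.05/0.119, about 0.2 to 0.4 SE. Simulated rates are about 4%, 5% and 6%.
- Extreme case with no within-centre noise. SE = √(1/5 + 1/9) = 0.56 between-centre SD, so the bias is about 0.5 to 0.9 SE. Simulated rates are about 7%, 10% and 14%.

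**4. Power: the plan's figure first**

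476/0.8 = 595 and 595/0.7 = 850 reproduce. The 476 itself is more than the stated inputs need: a two-sided 5% t test with 15 df (alpha and sidedness assumed) needs 364 for 90% power, and 475 gives 95%. That difference is on the safe side and is not part of this point.

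The calculation counts all 17 centres, which analysis 1 may not have. Take V = (1/k)(0.01 + 0.99/m) + (1/9)(0.01 + 0.99/28), with k EARLY centres and m patients in each, and df = k + 7. At d = 0.4:

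- k = 8, m = 28: V = 0.0107, d/√V = 3.87, power 95%.
- k = 6, m = 14: V = 0.0185, d/√V = 2.94, power 78%.
- k = 4, m = 14: V = 0.0252, d/√V = 2.52, power 63%.

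Analysis 3 keeps V = 0.0107. Power is 95% if the average effect stays at 0.4, 77% if it is diluted to 0.30, and 44% at 0.20. The centre counts, patient shares and dilution levels are assumptions.

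**The case against.** The plan is largely open about what it does. It uses the per-protocol label, contrasts it with intent-to-implement, says in the Discussion that this perspective focuses on successful centres, and pre-specifies the as-randomised comparison. All of that stands. What it leaves is an incorrect property claimed for the main analysis, and a choice of main analysis that lets the selected comparison govern the conclusion if the two differ.

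A reader might infer three stronger things that the documents do not support.

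- **That the bias must favour PCBH.** Nothing in the protocol says that readiness predicts better outcomes, and the extra support considered for low-fidelity centres would weaken any link between prior readiness and FID3. If every EARLY centre reaches FID3, no centre is lost and only the dropped pre-FID3 data remain.
- **That the false-positive rate for the patient outcome is 7 to 14%.** Those figures assume no within-centre noise. At the plan's ICC they are about 4 to 6%, with a bias that is small against d = 0.4.
- **That calendar time and baseline differences are left uncontrolled.** EARLY data after FID3 come later in period 1 than the DELAYED data as a whole, but calendar terms and baseline covariates are commonly left to an analysis plan, which is not shown. The protocol does collect a baseline for each centre. Such adjustment could reduce the problem, though it would not restore randomisation.

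**Conclusion.** The point holds as a misdescription and as a poor choice of main analysis. Analyses 1 and 2 are conditioned, in one arm only, on a post-randomisation judgement without an objective cutoff. They do not have the randomised-controlled property that the plan gives them, and the per-protocol label and the secondary analyses do not correct that.

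The size is uncertain. Under the assumed selection it is 0.27 to 0.49 between-centre SD, which is only 0.03 to 0.05 patient SD for WHODAS at ICC 0.01. Waiting time is the greater worry, because no ICC is given for it and because scheduling measures feed the fidelity judgement. The 7 to 14% false-positive range is an extreme case there, not an estimate. The direction is not established.

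**What to change.** - Make analysis 3 (all EARLY versus all DELAYED, period 1) the main analysis for average waiting time and for WHODAS superiority. Record this as a dated amendment before data analysis starts, which the protocol gives as May 2024.
- Keep analyses 1 and 2 as supportive per-protocol analyses. State that they are not protected by randomisation, and withdraw the claim of randomised controlled effects for them.
- Within analysis 1, adjust for each centre's pre-period baseline and for calendar month.
- Do not rely on randomised arm as an instrument for FID3, except as exploratory work. Partial implementation (FID2) may affect outcomes without FID3 being reached, so the exclusion assumption is doubtful.

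No new data are needed. The costs are a change of main analysis in a trial whose period 1 began in January 2022, and an as-randomised estimate that is diluted where fidelity is incomplete, with the loss of power shown above (77% at 0.30, 44% at 0.20).
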